## 2. Aim of Study

With this background in mind, we have planned a multicenter observational prospective cohort study involving some Italian Nephrology and Internal Medicine Units. The study aims to evaluate the effect of an SGLT2 inhibitor, Dapaglifozin, in Fabry disease patients with CKD stages 1–3. Specifically, the primary objective will be to determine the effect of Dapaglifozin on albuminuria, with a target of achieving a 20% reduction in albuminuria. As secondary aim, we will assess the effect of Dapaglifozin on kidney disease progression, measured by a reduction in eGFR < 3 mL/min/1.73 m^2^ per year and on clinical FD stability, defined by a FAbry STabilization indEX (FASTEX) score < 20 [30]. Additionally, any association of SGT2i with the progression of cardiac pathology, exercise capacity, kidney and inflammatory biomarkers, quality of life, and psychosocial factors will be evaluated.

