## 3. Methods

The study was approved by the Hospital Ethics Committee for Clinical Trials CESC (Ref No. 5499/AO/22). The primary and secondary end-points will include albuminuria, estimated GFR calculated using the CKD-EPI formula, septum ventricular diameter and diastolic function detected at echocardiography, left ventricular mass index/m^2^ and evolution of T1 mapping pattern at magnetic resonance imaging (MRI), FASTEX score, 5 Times Sit to Stand Test (5STS) [31], 6 Minute Walking Test (6MWT) [32], Cardiopulmonary Exercise Testing (CPET), quality of life and psychosocial questionnaires, and urinary tract infections. In addition, the dosage of exomes, IgG, IgG4, kidney injury molecule-1 (KIM-1), neutrophil-gelatinase-associated lipocalin (NGAL), liver-fatty-acid-binding protein (LFABP), isoprostane, tumor necrosis factor alpha (TNF-alpha), interleukin-1 (IL-1), and interleukin-6 (IL-6) will be tested. 

The study will enroll male and female subjects aged 18 years or older with CKD stages 1–3, a genetic and biochemical diagnosis of FD and albuminuria for at least 6 months despite treatment with a stable dose of ERT or Migalastat for at least 12 months and ACEi or ARB titrated to the maximum tolerated dosage for at least 6 months. The subjects with immunosuppressive therapy, type 1 diabetes mellitus, eGFR < 30 mL/min/1.73 m^2^, and recurrent urinary tract infections will be excluded. 

On the basis of previous evidence [24], we estimated that at least 28 patients would need to be recruited to answer the research question with a 95% level of confidence and a margin of error of 5%.

The study will last two years and will include baseline, 12-month, and 24-month visits. 

At the baseline visit, the demographic data (age, sex), anamnestic data (comorbidities, medications, underling kidney disease), and clinical parameters (blood pressure, heart rate, height, weight, Body Mass Index [BMI]) will be collected. Biochemical examinations (LysoGb3, hematocrit, hemoglobin, fasting glucose, creatinine, urea, cystatin C, sodium, potassium, calcium, phosphorus, uric acid, total proteins, albumin, vitamin D, parathormone, brain natriuretic peptide [BNP], troponin I, polymerase chain reaction [PCR], exomes, IgG, IgG4, KIM-1, NGAL, LFABP, isoprostane, IL-1, TNF-alpha, IL-6, and homocysteine) and a urinary sample (creatinine, albumin, urea, sodium, potassium, phosphate, proteins, urine test, urine cultures) will also be tested.

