Additionally, the patient will undergo an exercise capacity assessment by means of the 6MWT, 5STS, and CPET tests and a psychosocial assessment using the following questionnaires: brief Illness Perception Questionnaire (BIPQ), Morisky Medication Adherence Scale 8 (MMAS-8), Chronic Illness Anticipated Stigma Scale (CIASS), Experience in Close Relationship Scale—Short Form (ECR-S), Health Care Relationship Trust Scale Revised (HCR-TS), Difficult Doctor–Patient Relationship Questionnaire 10 (DDPRQ-10), General Anxiety Disorder 7 (GAD 7), Patient Health Questionnaire 9 (PHQ-9), Edmonton Symptom Assessment System revised (ESAS-r), Severity of Dependence Scale (SDS), and Insomnia Severity Index (ISI). The qualities of life will be investigated using the 36-Item Short-form Survey (SF36). Finally, electrocardiogram (ECG), echocardiography, and cardiac MRI will be performed.

During the 12-month visit, the medical history will be updated, clinical parameters will be recorded, blood and urine tests will be repeated, the exercise capacity will be assessed using 6MWT, 5STS, and CPET, and the FASTEX Index will be also compiled.

At the 24-month visit, all the assessments and examinations from the baseline visit will be repeated. 

The statistical analysis will be performed using SPSS 21.0. The continuous variables will be presented as means and standard deviations, or medians and interquartile ranges depending on their distribution, which will be assessed using histograms and QQ plots. The nominal variables will be reported as frequencies and percentages. To determine any possible associations between SGLT2i and the variables of the primary and secondary outcomes, Pearson and Spearman tests will be used for continuous variables, the Fisher exact test for nominal variables, and the Student or Mann–Whitney tests for continuous and nominal variables. Finally, ANOVA tests will be performed for multicategory variables. A *p*-value of less than 0.05 will be considered statically significant for all tests. 

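### The tests named for the drug's effect do not fit the design described: one cohort, three visits, no comparator, and no paired or repeated-measures method

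*Protocol article*

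**What the plan says.** **Design.** Section 2 (Aim of Study) states: "we have planned a multicenter observational prospective cohort study involving some Italian Nephrology and Internal Medicine Units". Its purpose is given as: "The study aims to evaluate the effect of an SGLT2 inhibitor, Dapaglifozin, in Fabry disease patients with CKD stages 1–3". The primary objective concerns albuminuria, "with a target of achieving a 20% reduction in albuminuria". The two secondary aims are thresholds: an eGFR loss below 3 mL/min/1.73 m² per year and a FASTEX score below 20.

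**Patients and visits.** Section 3 (Methods) gives one set of eligibility criteria, beginning "The study will enroll male and female subjects aged 18 years or older with CKD stages 1–3", and one minimum sample size, 28. It continues: "The study will last two years and will include baseline, 12-month, and 24-month visits". At 12 months "blood and urine tests will be repeated", and at 24 months the baseline assessments are done again in the same patients.

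**Analysis.** The same section says: "To determine any possible associations between SGLT2i and the variables of the primary and secondary outcomes, Pearson and Spearman tests will be used" on continuous variables. Fisher's exact test is assigned to nominal variables, and Student or Mann–Whitney to a continuous variable set against a nominal one. Then: "Finally, ANOVA tests will be performed for multicategory variables". Significance is p below 0.05 throughout.

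The article describes no untreated, comparator or dose-varying group. It names no paired, signed-rank, repeated-measures or mixed-model method.

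**The concern.** A fall in albuminuria from baseline in patients followed over two years is a within-patient change. The listed tests relate one variable to another across patients, or compare separate groups of patients. An association with SGLT2i needs some patients with the drug and some without, or at least varying exposure, and the article describes neither.

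At stake is the primary result. Followed as written, the sentence gives the analyst no test that validly answers the primary objective. The analyst must then improvise, and some obvious improvisations lose most of the information that 28 patients can supply.

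**Working it through.** The plan states no SD, correlation or power for albuminuria, so it has no figure of its own to reproduce here. The check takes each way of applying the sentence in turn.

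**Inputs from the article:** n = 28, three visits, a 20% reduction, significance level 0.05.

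**Assumptions:** two-sided testing (sidedness is not stated); log-scale SD of albuminuria 0.8 to 1.2; between-visit correlation rho 0.5 to 0.9; the 20% reduction read as a ratio of 0.80, so the log-scale effect is ln 0.80 = −0.223.

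**Reading 1: everyone takes the drug and SGLT2i is the variable.** Exposure has zero variance, so a correlation with it is 0/0. Run on 28 patients with a constant exposure, Pearson and Spearman return no value. Student and Mann–Whitney have an empty second group and also return no value. Fisher's table has an empty row, giving an undefined odds ratio and p = 1.

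**Reading 2: visit is the grouping variable.**

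- Independent-sample SE of the difference: SD × sqrt(2/n)
- Paired SE: SD × sqrt(2(1 − rho)/n)
- Ratio: 1/sqrt(1 − rho), which is 1.83 at rho 0.7 and 2.24 at rho 0.8

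With SD 1.2, rho 0.8 and n = 28:

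- Independent: 1.2 × sqrt(2/28) = 0.321, and 0.223/0.321 = 0.70 standard errors
- Paired: 1.2 × sqrt(0.4/28) = 0.143, and 0.223/0.143 = 1.56 standard errors

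Simulated power for a 20% reduction, two visits, 20,000 replicates per cell (independent t / paired t):

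| log SD | rho 0.5 | rho 0.7 | rho 0.8 | rho 0.9 |
|---|---|---|---|---|
| 0.8 | 0.105 / 0.297 | 0.054 / 0.453 | 0.032 / 0.607 | 0.009 / 0.888 |
| 1.0 | 0.057 / 0.207 | 0.027 / 0.312 | 0.012 / 0.441 | 0.002 / 0.723 |
| 1.2 | 0.040 / 0.162 | 0.013 / 0.226 | 0.005 / 0.323 | 0.001 / 0.561 |

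With no true change, the independent test rejects in at most 0.7% of trials (rho 0.5) and in 0.01% or fewer at rho 0.8 and above, against a nominal 5%. The paired test stays at 4.7% to 5.3%. One-way ANOVA across three visits, treated as independent groups, rejects in 0.4% at rho 0.5 and 0.01% or fewer from rho 0.7 upward.

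**Reading 3: all visit records are pooled in a correlation with a patient-level variable.** This gives 28 × 3 = 84 records. Treated as 84 patients, the type I error rises to 0.165 at rho 0.5 and 0.255 at rho 0.9. The direction of the error therefore depends on how the tests are used.

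**Reading 4: an untreated group exists.** The tests are then defined. But the group is not described, and an unadjusted comparison mixes the drug's effect with the reasons it was prescribed.

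**The case against.** **A comparator may be intended.** The study is observational, the eligibility criteria do not require taking dapagliflozin, and medications are recorded at baseline. The test list is the usual one for exposed against unexposed patients. This stands so far as it goes: constant exposure is inferred from the absence of any comparator, not stated. It does not rescue the plan, because the group would be undescribed and the tests unadjusted.

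**The tests have valid uses.** One record per patient, such as change in albuminuria or meeting a threshold, could be related to sex or type of Fabry therapy with these same tests. That is correct, but it does not estimate the drug's effect, which is the purpose the sentence gives.

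**Student and ANOVA have paired or repeated-measures forms.** They do. The article, however, ties Student to a continuous variable split by a nominal one, alongside Mann–Whitney, and ANOVA to multicategory variables. Pearson, Spearman, Fisher and Mann–Whitney would remain unsuited in any case.

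**An article leaves detail to the analysis plan.** True of omissions. Here specific tests are assigned to a specific purpose, including the primary outcome, and they do not match the design.

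**Stronger readings that the documents do not support.** A reader might infer that the study will treat visits as independent groups and so has under 1% power. The article never says so, and that is only one way of applying the sentence. A reader might also infer that histograms and QQ plots of about 28 values decide between parametric and rank tests. The article ties those plots only to how continuous variables are summarised, as mean and SD or median and interquartile range.

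**Conclusion.** The point holds. The named tests do not estimate within-patient change, and no comparator is described that would give them another valid role for the stated purpose. This is wrong as written, not merely condensed, and should be corrected before analysis.

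That conclusion needs no assumed number. The size does. If visits are compared as independent groups, power for a 20% reduction is 0.1% to 10.5% over the assumed range, against 16% to 89% paired. These figures are conditional on that use and on an SD and correlation that the article does not give. For any positive correlation, the independent-sample SE for a visit comparison is too large.

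Pairing restores a valid test; it does not guarantee adequate power with 28 patients. Without a comparator it also estimates change on treatment and cannot by itself attribute that change to the drug.

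**What to change.** Replace the sentence on associations with a within-patient analysis.

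- **Primary endpoint:** a linear mixed model for log urinary albumin-to-creatinine ratio, with visit (0, 12, 24 months) as fixed effect and patient as random effect, or a paired analysis. Report the geometric mean ratio to baseline with its 95% CI and set it against 0.80. If the 20% target is meant as a per-patient threshold, say so and report the proportion reaching it with an exact 95% CI.
- **Continuous secondary endpoints measured at baseline and follow-up:** the same approach.
- **Threshold endpoints (eGFR loss below 3 mL/min/1.73 m² per year; FASTEX below 20):** proportions with exact 95% CIs. A paired before-and-after test of proportions would not suit them, because annual eGFR loss has no baseline value and the article lists FASTEX only at the 12-month visit.
- **If a comparator exists:** describe who is in it, and use a baseline-adjusted group contrast that also adjusts for confounders.

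Urinary albumin and creatinine are already collected at the visits. With no comparator, the cost is a change of wording and no new data. With one, the group and its confounders must also be specified.

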## 4. Conclusions

This study will be the first in the literature to evaluate the effect of Dapaglifozin in patients with albuminuria affected by CKD secondary to Fabry’s disease, primarily on renal outcomes (albuminuria and CKD progression) and, secondarily, on cardiovascular outcomes, exercise capacity, and quality of life. It will provide new compelling evidence on the use of SGLT2 inhibitors in the field of rare diseases.

## Data Availability

Not available. Further inquiries can be directed to the corresponding author.
